## Abstract

**Background:**

Non-small cell lung cancer is the most common type of lung cancer. Surgery is proven to be the most effective treatment in early stages, despite its potential impact on quality of life. Pulmonary rehabilitation, either before or after surgery, is associated with reduced morbidity related symptoms and improved exercise capacity, lung function and quality of life.

**Methods:**

We describe the study protocol for the open-label randomized controlled trial we are conducting on patients affected by primary lung cancer (stages I-II) eligible for surgical treatment. The control group receives standard care consisting in one educational session before surgery and early inpatient postoperative physiotherapy. The treatment group receives, in addition to standard care, intensive rehabilitation involving 14 preoperative sessions (6 outpatient and 8 home-based) and 39 postoperative sessions (15 outpatient and 24 home-based) with aerobic, resistance and respiratory training, as well as scar massage and group bodyweight exercise training.

Assessments are performed at baseline, the day before surgery and one month and six months after surgery. The main outcome is the long-term exercise capacity measured with the Six-Minute Walk Test; short-term exercise capacity, lung function, postoperative morbidity, length of hospital stay, quality of life (Short Form 12), mood disturbances (Hospital Anxiety and Depression Scale) and pain (Numeric Rating Scale) are also recorded and analysed. Patient compliance and treatment-related side effects are also collected. Statistical analyses will be performed according to the intention-to-treat approach. T-test for independent samples will be used for continuous variables after assessment of normality of distribution. Chi-square test will be used for categorical variables. Expecting a 10% dropout rate, assuming α of 5% and power of 80%, we planned to enrol 140 patients to demonstrate a statistically significant difference of 25 m at Six-Minute Walk Test.

**Discussion:**

Pulmonary Resection and Intensive Rehabilitation study (PuReAIR) will contribute significantly in investigating the effects of perioperative rehabilitation on exercise capacity, symptoms, lung function and long-term outcomes in surgically treated lung cancer patients. This study protocol will facilitate interpretation of future results and wide application of evidence-based practice.

**Trial registration:**

ClinicalTrials.gov Registry n. NCT02405273 [31.03.2015].

## Background

Lung cancer accounts for a fifth of the total global burden of disability-adjusted life years due to cancer [1]. Non-small cell lung cancer (NSCLC) is the most prevalent type of all lung cancers [1], with surgical resection appearing to be the most effective treatment in early stages (Stages I and II) [2].

Although surgical resection results in higher survival rates [3], it is associated with significant morbidity, functional limitations and decreased quality of life (QoL) [4].

Long-term physical impairment is an important and undesirable consequence of surgery, limiting patients’ recovery to a greater extent than do other severe pulmonary complications, such as atelectasis, dyspnoea and pneumonia [2, 5]. Furthermore, chronic obstructive pulmonary disease (COPD) is frequent in lung cancer patients and is associated with increased postoperative morbidity and mortality [6–8].

Recent studies suggest that perioperative pulmonary rehabilitation (PR) programmes including exercise may improve exercise capacity, functional performance and QoL, both pre- and postoperatively [2, 9].

PR is a comprehensive intervention that includes exercise training (endurance and resistance), education and behaviour changes [10, 11]. PR is also part of the new integrated pathways for enhanced recovery, where it has shown to improve patient satisfaction and to reduce in-hospital stay [12].

Surgical candidates seem to benefit from preoperative PR. In COPD patients, preoperative PR is correlated with improvement in functional parameters, which in turn may increase resection rate and allow more extensive lung resections [3, 10].

It is well known that exercise training is associated with significant increase in peak oxygen consumption (VO2peak) [13–15], which has been confirmed as a strong independent predictor of perioperative or postoperative complications and overall long-term survival for individuals with NSCLC [11, 16]. Indeed, patients with reduced exercise tolerance and low VO2peak show poorer thoracic surgical outcomes [11, 16]. Therefore, preoperative PR could reduce symptoms and morbidity, shorten hospital stay and lower healthcare costs [17, 18].

Concerning postoperative PR, recent literature supports improvement in exercise capacity through physical training [5, 19], whereas there is not sufficient evidence supporting meaningful clinical changes in lung function [5, 9, 19, 20]. The effectiveness of postoperative PR on QoL is still controversial, although some studies suggest that exercise training could be advantageous for some domains of QoL [19, 20].

Both pre- and postoperative PR tailored to lung cancer patients has been demonstrated to be safe and feasible [21, 22], although research conducted in this field presents dissimilarities concerning type of intervention, intensity, setting and timing [2, 5].

An updated, extensive literature review on perioperative physical exercise interventions was conducted by our group to establish the most updated and evidence-based interventions for patients undergoing surgery for NSCLC [23]. Based on its results, the best available evidence supports the inclusion of high intensity aerobic training for upper and lower limbs (primarily cycling and/or walking) and respiratory exercise (primarily inspiratory muscle training) in the perioperative period. Postoperative programmes should also include strength training and balance training. Therapeutic interventions can be conducted in both outpatient and home-based settings. Although this review focused on the exercise components of rehabilitation, most treatment protocols also include routine physiotherapy with dyspnoea management and airway clearance techniques. With regards to the length of interventions, while the duration of the preoperative phase is strictly determined by the time of elective surgery, postoperative intervention ranges from 6 to 20 weeks.

In summary, systematic reviews conducted in this field advocate the value of both pre- and postoperative PR programmes, with aerobic training as the most relevant component. However, this literature demonstrates that primary research validity has been limited by poor methodological quality and small and heterogeneous samples of clinical studies [2, 5, 23]. Thus, there is the need to build stronger evidence regarding the effectiveness of evidence-based PR interventions in this population.

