## Methods

### Study design

A single institution 1:1 randomized controlled open-label trial with two parallel arms, powered for superiority, has been designed in accordance with the CONSORT statement and Helsinki declaration. The study has been approved by the local Ethical committee [n. 2013/0009390] and funded by the Italian Ministry of Health [GR-2011-02351711].

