### Participants and setting

All patients with highly suspicious or diagnosed primary NSCLC are screened for eligibility criteria within the Lung Cancer Multi-Disciplinary Team Meeting at Arcispedale Santa Maria Nuova (ASMN) of Reggio Emilia, Italy. This is an Institute for Advanced Technologies and Healthcare Protocols in Oncological Research certified by the Organization of European Cancer Institutes in 2014. The Thoracic Surgery Unit’s catchment area covers a range of about 535,000 inhabitants and performs an average of 500 operations per year, including about 130 lung resections for malignancies.

Patients with Stages I and II NSCLC are considered for enrolment if they qualify for surgery. We exclude candidates who require adjuvant therapies and patients unfit for the physical exercise required by intervention [Table 1]. In patients affected by COPD, medical treatment is reviewed and optimized according to the most recent Global Initiative for Chronic Obstructive Lung Disease guidelines at the start of the selection process, to minimize confounding factors.

**Table 1 Tab1:** Inclusion and exclusion criteria

Inclusion criteria	Exclusion criteria
Patients affected by NSCLC in Stage I-II	Tumour stage requiring adjuvant therapies
Patients eligible for lung resection	Patients unfit for the type of physical exercise included in study protocol
Patients able to walk autonomously without medical devices (e.g., crutches)	Patients affected by sensorial or cognitive deficits with potential severe impact on compliance (deafness, blindness, dementia, etc.)
Patients able to give informed consent	

Written informed consent is obtained from participants by the operating surgeon during the preoperative consultation. Subsequently, patients undergo baseline assessment and afterwards are randomized to receive intensive PR (Intervention Group - IG) or SC (Control Group - CG) (Fig. 1).

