### Statistical considerations

#### Sample size

Since data for mean and standard deviations of 6MWT after lung surgery with or without treatment have never been published, Cohen’s medium effect size (d = 0.5) has been used to compute sample size based on the minimal significant variation reported (25 m) [33].

We also expect a potential dropout rate of about 10% for the aforementioned reasons. Thus, assuming 5% type I error and 80% power for this study, we plan to enrol 140 patients (about 70 patients in each arm).

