#### Statistical analysis

Statistical analyses will be performed according to the intention-to-treat approach. Statistical techniques per study aims are as follows:
*Primary aim:* t-test for independent samples to compare the mean of the change (defined as T3 – T0 related date) in 6MWD between IG and CG. In case of heteroscedasticity, checked by folded F test, the Satterthwaite adjustment will be used.
*Secondary aims*:- t-test for independent samples to compare the mean of the change between IG and CG for 6MWD (T2 – T0 change), FEV1, FVC, DLCO and SF-12 score (T3 – T0 change), HADS score (T1 - T0 and T3 - T0), NRS score (T2 – T0 and T3 – T0) and LoS. In case of heteroscedasticity, checked by folded F test, the Satterthwaite adjustment will be used.- chi-square test to compare the proportion of postoperative complications between IG and CG;

Five percent significance will be used to assess the *p*-values and 95% two-sided confidence interval will be provided for each tested parameter; the confidence intervals will be calculated assuming normal distribution.

Statistical calculations will be performed by the local Research and Statistics Unit using SAS System release 9.2 or later, R release 3.3.3 or later, SPSS release 23 or later, according to the availability at the time of the data analysis.

Patient adherence to protocol may be a crucial issue in determining the efficacy of rehabilitation programmes, including exercise training. Although it has not been plainly demonstrated, in principle, non-attendance could affect exercise dose and influence the outcome of treatment [34]. Therefore, if patient compliance, is less than 80% [25], we will proceed with a second per-protocol analysis.

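### The complication comparison uses a crude chi-square although COPD, which the protocol links to postoperative morbidity, is identified before randomisation; stratifying by it would be a small, cheap improvement

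*Protocol article*

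**What the plan says.** The Background of the protocol article states that "chronic obstructive pulmonary disease (COPD) is frequent in lung cancer patients and is associated with increased postoperative morbidity and mortality". Under Participants and setting, medical treatment of patients with COPD is reviewed "at the start of the selection process, to minimize confounding factors". Consent, baseline assessment and randomisation come after that step. Table 2 schedules pulmonary function tests for every patient at baseline (T0).

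The Statistical analysis section fixes a "chi-square test to compare the proportion of postoperative complications between IG and CG" and says that a "95% two-sided confidence interval will be provided for each tested parameter". It mentions no covariate or stratum for this outcome. The Randomization procedure section describes a list prepared in advance and names no stratification factor.

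Complications are a secondary outcome. The sample size is built on the six-minute walk distance alone.

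**The concern.** The protocol regards COPD as common and as linked to the very outcome tested here, and it treats COPD as a potential confounder at selection. Reviewing medication does not make the number of COPD patients equal in the two arms. The named analysis then makes no use of the information.

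Two things are at stake, both limited to this secondary outcome. First, if the baseline table shows a visible COPD imbalance, the crude result will be hard to interpret. An adjustment chosen at that point, in an open-label trial, would be open to criticism. Second, outcome variation explained by COPD stays in the error of the crude comparison, which costs some precision.

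This is not a gap that an unseen analysis plan might simply fill, because the article names the test.

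**Working it through.** **The plan's own figure.** The design is "A single institution 1:1 randomized controlled open-label trial with two parallel arms"; a "medium effect size (d = 0.5) has been used to compute sample size", and "assuming 5% type I error and 80% power for this study, we plan to enrol 140 patients (about 70 patients in each arm". With two-sided α = 0.05:

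- n per arm = 2 × (1.960 + 0.842)² / 0.5² = 62.8, so 63.
- Allowing for 10% dropout: 63 / 0.90 = 70 per arm, 140 in total.

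The stated 140 reproduces. It gives 63 evaluable patients per arm, or 70 if everyone randomised contributes complication data.

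**Inputs not in the documents (assumed).** COPD prevalence p of 30 to 50%; simple randomisation; complication risk with and without COPD of 50% and 20% (strong case, odds ratio (0.5/0.5)/(0.2/0.8) = 4) or 30% and 20% (weak case, odds ratio (0.3/0.7)/(0.2/0.8) = 1.7); for power, an intervention that halves the risk.

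**Chance imbalance in COPD.** SD of the difference between arms = √(2p(1−p)/n).

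| n per arm | p | SD (points) | P(gap ≥ 10 points) | P(gap ≥ 15 points) |
|---|---|---|---|---|
| 63 | 0.30 | 8.2 | 22% | 7% |
| 63 | 0.50 | 8.9 | 26% | 9% |
| 70 | 0.30 | 7.7 | 20% | 5% |
| 70 | 0.50 | 8.5 | 24% | 8% |

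**What such a gap does.** In the strong case, a 10-point gap shifts the crude risk difference by 0.10 × (50 − 20) = 3 points. Overall risk is 0.3 × 50 + 0.7 × 20 = 29%, or 35% at p = 0.5. The standard error of the difference is √(2 × 0.29 × 0.71/63) = 8.1 points, or 8.5 points at 35%. The shift is therefore 3/8.1 = 0.37 or 3/8.5 = 0.35 of a standard error.

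**Type I error.** By simulation, the crude chi-square rejects in 4.8 to 5.3% of null trials across all settings examined. Among only those null trials with a COPD gap of 10 points or more (strong case, 63 per arm), it rejects in a little over 7%, against about 5% for the stratified test. With a COPD odds ratio of 2 or less, the corresponding crude figure is 5.0 to 5.7% (70 per arm).

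**Precision.** The share of outcome variance explained by COPD is p(1−p)(r₁ − r₀)² / [r(1−r)], where r₁ and r₀ are the risks with and without COPD and r is the overall risk.

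- Strong case, p = 0.3: 0.21 × 0.09 / (0.29 × 0.71) = 9.2%.
- Strong case, p = 0.5: 0.25 × 0.09 / (0.35 × 0.65) = 9.9%.
- Weak case, p = 0.3: 0.21 × 0.01 / (0.23 × 0.77) = 1.2%.
- Weak case, p = 0.5: 0.25 × 0.01 / (0.25 × 0.75) = 1.3%.

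Simulation of the Mantel-Haenszel against the crude risk difference agrees: the null variance ratio, crude to stratified, is 1.09 to 1.10 in the strong case and about 1.00 in the weak case.

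**Power for a halved risk, 63 per arm.** In the strong case it goes from about 50 to 53% (p = 0.3) and from about 62 to 64% (p = 0.5). In the weak case the change is under 1 point. A separate set of runs with 70 per arm and a treatment odds ratio of 0.4 gives a change of −0.6 to −0.1 points at a COPD odds ratio of 1.5, −0.1 to +0.2 at 2, +1.0 to +1.7 at 3 and +1.5 to +3.1 at 4.

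**The case against.** A reader might infer that the crude chi-square is invalid, or that COPD biases the comparison. The documents do not support that. Randomisation makes chance imbalance part of what the 5% error rate already covers, and the simulations confirm it. Imbalance matters only for reading a single trial in which it happens to occur, and even then a 10-point gap moves the estimate by little more than a third of a standard error.

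A reader might also infer that COPD is the only driver of complications the protocol recognises, or that it is shown to be uncontrolled by design. Neither holds. The Background calls peak oxygen consumption a strong predictor of complications as well, although Table 2 does not list it as an assessment. The randomisation section is silent on stratification and the article is condensed, so stratification is not stated rather than absent. If the list were stratified by COPD, imbalance would be a smaller worry, but the analysis should then follow the design.

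Three further objections stand. The gain depends on inputs that the article does not give, and the favourable figures need a COPD odds ratio of about 3 or more. No section defines COPD or lists COPD status as a study variable, so its availability has to be confirmed. The outcome is secondary and did not determine the sample size.

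What these objections do not remove is that the protocol names the factor, identifies it before allocation, and then fixes a test that leaves it out.

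**Conclusion.** The point holds as a minor missed opportunity in a secondary analysis. The chi-square is a valid test and nothing in the primary analysis or the sample size changes. Under the assumed prevalence of 30 to 50%, a COPD gap of 10 points or more would occur in about 20 to 26% of trials of this size. Stratifying would bring between no gain (risks of 30% and 20%) and about 2 to 3 points of power with 9 to 10% lower null variance (risks of 50% and 20%). Where in that range this trial lies cannot be settled from the documents. The firmer argument is pre-specification: if an imbalance does appear, the adjusted comparison will already have been chosen.

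**What to change.** In the Statistical analysis section, keep the complication endpoint as defined. Make its main comparison a Cochran-Mantel-Haenszel test stratified by COPD status before randomisation, with the Mantel-Haenszel risk difference and its 95% confidence interval, and report the crude chi-square alongside. Take COPD status as identified at selection and confirm it from the T0 pulmonary function tests.

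The cost is a short change of wording, made before the outcome data are examined, plus a written definition of COPD and a check that each patient's status can be fixed from pre-allocation records. It needs no additional patients or visits. The downside is that the gain may be negligible, or power very slightly lower, if COPD turns out to be only weakly prognostic.

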### Rationale

The literature review provided sufficient evidence to justify a clinical trial to investigate the effects of pre- and postoperative intensive rehabilitation in patients affected by NSCLC undergoing surgical resection. Pulmonary Resection and Intensive Rehabilitation (PuReAIR) randomized controlled trial is designed to assess the effect of intensive PR on improving exercise capacity measured with the Six-Minute Walk Test (6MWT) in such patients.

The effects of intensive PR on postoperative morbidity, length of hospital stay (LoS), QoL, pain, depression and lung function will also be recorded.

The study protocol provides a detailed description of the interventions to accurately interpret results, which will be published on completion.

### Study objectives

#### Primary aim

The primary aim of this study is to investigate the effectiveness of intensive PR on exercise capacity in surgically treated NSCLC patients six months after surgery.

##### 1.2.1.1.Primary outcome measure

The primary outcome measure to assess the superiority of intensive PR over standard care (SC) is the change in distance walked in six minutes (6MWD) measured six months after surgery, compared to baseline.

#### Secondary aims

The secondary aims of this study are to investigate the effectiveness of intensive PR on:Short-term exercise capacityLung functionPostoperative complicationsLength of hospital stayQuality of lifeMood disturbancesPain

#### Secondary outcome measures

The secondary outcomes are:Change in 6MWD measured one month after surgery and compared to baselineForced expiratory volume in 1 s (FEV1), forced vital capacity (FVC) and diffusing lung capacity for carbon monoxide (DLCO) measured six months after surgery and compared to baselinePostoperative complications registered one month and six months after surgery as specific eventsInterval (in days) between the date of the operation and the date of dischargeChange in Short Form 12 questionnaire (SF-12) scores measured six months after surgery and compared to baselineChange in Hospital Anxiety and Depression Scale (HADS) score measured the day before surgery and six months after surgery, compared to baselineChange in Numeric Rating Scale (NRS) score measured one month and six months after surgery, compared to baseline.

### Additional assessments

Data regarding patient compliance and treatment-related side effects during both preoperative and postoperative intensive PR will also be collected.

Intensive PR includes the implementation of hospital-based and home-based training. Patients randomized to the treatment group are requested to register the activities performed at home on a training log; distance in kilometres, number of steps and heart rate achieved during aerobic walking and exercises performed during respiratory muscle training (RMT) session are recorded. As patient adherence to protocol is a crucial issue in rehabilitation and the literature recommends the consistent and explicit reporting of exercise attendance in people with respiratory diseases [24], the proportion of training sessions performed are collected to assess patient compliance: adherence to the protocol is defined as the achievement of 80% or more of the training exercises prescribed [25].

We consider as minor side effects self-reported pain or discomfort in the muscles/joints involved with the physical component of the treatment; major side effects include any trauma secondary to a fall requiring specific interventions or symptomatic alterations of the basic vital signs (i.e., blood pressure, heart rate) arising during or shortly after the end of exercise and confirmed by instrumental measurement.

To evaluate the actual effect of lung resection on the study population before the postoperative treatment, FEV1, FVC and DLCO are also registered in the experimental group one month after surgery and compared to baseline.

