### Measurements

Patients included in the study are assessed at baseline (T0), the day before surgery (T1), one month after surgery (T2) and six months after surgery (T3) [Table 2].

**Table 2 Tab2:** Assessments

	T0 Baseline	Randomization	T1 1 day before surgery (14÷21 days from baseline)		T2 (1 month ± 5 days after surgery)		T3 (6 months ± 5 days after surgery)	
			IG	CG	IG	CG	IG	CG
Pulmonary function (PFTs)	x		x				x	x
Exercise capacity (6MWT)	x				x	x	x	x
Quality of life (SF-12)	x						x	x
Mood disturbances (HADS)	x	Randomization	x	x			x	x
Pain (NRS)	x				x	x	x	x
Length of stay					x	x		
Postoperative complications					x	x	x	x

*IG* Intervention Group, *CG* Control Group, *PFTs* Pulmonary Function Tests, *6MWT* Six-Minute Walk Test, *SF-12* Short form 12, *HADS* Hospital Anxiety and Depression Scale, *NRS* Numeric Rating Scale

Baseline assessments are carried out immediately before randomization (T0) and include lung function, exercise capacity, QoL, mood disturbances and pain.

Static and dynamic respiratory volumes and DLCO are measured with full pulmonary function tests (PFTs). Exercise capacity is evaluated with 6MWT, according to current guidelines [11, 26]. Data on QoL are assessed with SF-12 [27], mood disturbances are evaluated using the HADS [28] and pain is quantified using the NRS [29].

The day before surgery (T1), all patients are re-assessed for mood disturbances. PFTs are repeated in the IG; treatment-related side effects and patient adherence to the intensive preoperative PR are also recorded.

One month after surgery (T2), patients repeat exercise capacity and pain evaluation using the same tools employed at baseline (T0). Data regarding LoS, postoperative complications and 30-day mortality are also recorded at this stage. Postoperative complication categories include acute respiratory failure, cardiac failure (including myocardial infarction), surgical site infection (including pneumonia and bronco-pleural fistula), arrhythmias (including atrial fibrillation), thrombosis and pulmonary embolism, neurological impairment (including stroke) and other (specified).

Long-term follow-up takes place 6 months after surgery (T3) and includes the assessment of lung function, exercise capacity, QoL, mood disturbances, pain and late postoperative complications. In the IG, patient adherence to the intensive postoperative PR and side effects are also recorded at 6 months.

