#### Intervention group

Patients allocated to the IG receive SC plus intensive PR, which includes a total of 53 sessions (14 preoperative and 39 postoperative).

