##### 2.4.2.1.Preoperative intensive PR

Preoperative intensive PR is organised into six outpatient sessions performed two to three times per week, plus eight home-based sessions performed three to four times per week. The overall duration of this treatment ranges from 14 to 21 days, starting the same day the patient is listed for surgery or immediately afterwards, to minimize the delay in offering surgical treatment and to avoid the 30-day breach, as recommended by the regional guidelines [32].

Each outpatient session lasts approximately two hours and consists of an individual, supervised and personalised combination of the following elements:Therapeutic education, whose contents are the same as those provided to CG. It is delivered during the first outpatient session and repeated, if necessary, during the course of the treatment.Aerobic training, which consists of 30 to 40 min on a cycle ergometer. This training is maintained at the intensity of 60–80% peak workload (previously determined with shuttle walking test) [30] and includes a 5-min warm up and a 5-min cool down. Within this range, the intensity of training is adapted to the patient’s tolerance.Resistance training for lower limbs (extensor muscle group), upper limbs (biceps, triceps, deltoids, latissimus dorsi, pectoralis) and abdominal wall. Each exercise is performed for two to three sessions of 10 repetitions at the maximal load (previously determined with the 10-repetition maximum test) [31];RMT which includes breathing pattern training, PEP training and inspiratory muscle training for at least 15 to 30 min. Inspiratory muscle training is performed by means of a pressure threshold device, with a load ≥30% of maximal predicted inspiratory pressure; intensity is adapted to the patient’s tolerance.

Each home-based session lasts approximately one hour and consists of an individual, unsupervised and personalised combination of RMT, performed twice a day, plus 30 min of aerobic walking at the intensity of 60–80% of maximal heart rate. Patients are given a portable pedometer and a heart rate monitor and are requested to record their adherence to home-based training in the training log, which collects kilometres, steps and heart rate achieved during aerobic walking and exercises performed during RMT session.

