##### 2.4.2.2.Postoperative intensive PR

Postoperative PR starts one month after surgery and includes 39 sessions divided into 15 outpatient sessions performed twice a week and 24 home-based sessions performed three times per week. Overall, the postoperative PR programme lasts 8 weeks.Each outpatient session takes approximately two hours and 15 min and includes both aerobic and resistance training, following the same procedures described for preoperative PR, plus RMT for the first eight sessions. In addition, outpatient postoperative PR includes 10 min of scar massage during the first four weeks and group bodyweight exercise training, scheduled once a week for the entire duration of the programme.Each home-based session lasts approximately one hour and consists of an individual, unsupervised and personalised combination of RMT performed twice a day and 30 min of aerobic walking at the intensity of 60–80% of maximal heart rate, monitored by patients with the portable device provided. Once again, patients are requested to record their adherence to home-based training by the training log.

At the end of postoperative PR, patients are advised to continue aerobic training and RMT until the 6-month follow-up is completed (T3).

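### Symptomatic blood-pressure changes in unsupervised home sessions (32 of 53), and other exercise-related symptoms in any setting, fit neither side-effect class as defined, so side effects may be under-ascertained

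*Protocol article*

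**What the plan says.** **Definitions.** Additional assessments in the protocol article says that side effects of both the preoperative and the postoperative programme are collected, and it excludes no setting. Minor side effects are self-reported pain or discomfort in the muscles or joints involved. Major side effects include two things joined by *or*: trauma from a fall that needs specific intervention, and changes in vital signs that cause symptoms, where the condition set is "i.e., blood pressure, heart rate) arising during or shortly after the end of exercise and confirmed by instrumental measurement".

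**Setting.** The Intervention group section describes a programme "which includes a total of 53 sessions (14 preoperative and 39 postoperative"). The preoperative part is "six outpatient sessions performed two to three times per week, plus eight home-based sessions performed three to four times per week". The postoperative part is "39 sessions divided into 15 outpatient sessions performed twice a week and 24 home-based sessions performed three times per week". A home session "consists of an individual, unsupervised and personalised combination of RMT, performed twice a day, plus 30 min of aerobic walking".

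**Equipment and log.** For home training, "Patients are given a portable pedometer and a heart rate monitor". In the postoperative part, walking intensity is again followed with the portable device supplied. The log is described as holding kilometres, steps, heart rate and the respiratory exercises done.

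**Recording.** According to Measurements, side effects of the preoperative part are recorded the day before surgery (T1). For the postoperative part, "In the IG, patient adherence to the intensive postoperative PR and side effects are also recorded at 6 months". That part starts one month after surgery, and "Overall, the postoperative PR programme lasts 8 weeks".

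**The concern.** Side effects are the tolerability evidence for an intensive exercise programme given shortly before, and again from one month after, lung resection. The two classes do not cover the events one would most want to know about. One limb of the major class depends on a measurement, and for blood pressure no means of making it is named for the setting where most sessions take place. An event that fails this condition does not drop to minor, because minor is confined to muscle and joint complaints. It has no class at all. The same is true of exercise-related symptoms that are neither musculoskeletal, nor fall trauma, nor a confirmed change in blood pressure or heart rate.

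A low side-effect count under these rules would not separate a well-tolerated programme from events that had nowhere to be counted. The article looks ahead to wide application of the results, so the distinction matters.

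**Working it through.** **1. Session count.** Inputs are from Intervention group and sections 2.4.2.1 and 2.4.2.2.

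| Phase | Outpatient | Home | Total | Home share |
|---|---|---|---|---|
| Preoperative | 6 | 8 | 14 | 8/14 = 57.1% |
| Postoperative | 15 | 24 | 39 | 24/39 = 61.5% |
| Both | 21 | 32 | 53 | 32/53 = 60.4% |

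The stated total of 53 is reproduced: (6 + 8) + (15 + 24) = 53.

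**2. Events set against the definitions.**

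| Event during or shortly after exercise | Outpatient | Home |
|---|---|---|
| Muscle or joint pain | minor | minor |
| Fall trauma needing intervention | major | major |
| Symptomatic heart-rate change | major if measured | major if measured; monitor supplied |
| Symptomatic blood-pressure change | major if measured | no class unless measured by other means; no device named |
| Dyspnoea, chest pain, desaturation or syncope without injury, with no confirmed change in blood pressure or heart rate | no class | no class |

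The gap has two parts: blood pressure at home, and other symptoms everywhere.

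**3. How large could the blood-pressure part be?** The documents give no event rates, so this shows a range and is not an estimate. Assume that the true rate of major-type events per session is the same at home and in outpatient sessions. Assume also that a share q of the home events could qualify only through blood pressure and is never measured. Then

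share of major-type events counted = 1 − (32/53) × q

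| q | 0 | 0.25 | 0.5 | 0.75 | 1 |
|---|---|---|---|---|---|
| Counted | 100% | 85% | 70% | 55% | 40% |

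The equal-rate assumption is open to challenge. Preoperative outpatient sessions last about 2 h, postoperative ones about 2 h 15 min and home sessions about 1 h. If risk follows time, the home share is 32/(6 × 2 + 15 × 2.25 + 32) = 32/77.75 = 41%. The share counted is then 1 − 0.41q, which is 59% at q = 1. Under either assumption the loss is nil at q = 0.

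**4. Timing of the stated record.** From T2 to T3 is five months, about 5 × 4.35 = 21.7 weeks. The postoperative programme takes the first 8 of these, so T3 falls about 21.7 − 8 = 13.7 weeks after it ends. This matters only for events not noted on some earlier occasion, and the article neither says that they are noted earlier nor rules it out.

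**The case against.** Several points on the other side stand, and they limit the finding.

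- A reader might infer that every major side effect needs instrumental confirmation. The text does not support this. Fall trauma is a separate limb and, on the natural reading, needs no vital-sign measurement.
- A reader might infer that confirmation is mostly impossible at home. For heart rate, one of the two named signs, patients have a monitor and log the readings.
- A blood-pressure event at home is not excluded in principle. The time limit applies to when the change arises, and no place, operator or device is laid down for the confirmation. An attending clinician's measurement, or one on the patient's own device, would satisfy it.
- Recording at six months does not show that events are first asked about then. The same sentence covers adherence, which comes from a log kept throughout, and patients meet staff at 15 outpatient sessions during the programme. Reliance on late recall is possible but not shown.
- Postoperative complications are recorded in both arms at T2 and T3, with categories for respiratory failure, cardiac failure, arrhythmia, stroke and a specified other. This will catch some serious events. It does not cover the preoperative phase, is not aimed at milder symptoms, and does not label events as exercise-related.
- The article is condensed. The layout of the log and a wider adverse-event procedure may be in the full protocol, so the absence of a symptom field from the article is not itself an error.
- Side effects are an additional assessment, not a primary or secondary outcome, and no between-arm test depends on them.

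What remains is the definition that the article itself states. The word *include* may mean that the list of major events is not exhaustive, but other events would then still have no stated class.

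**Conclusion.** The point holds as a limited defect of definition. As written, a symptomatic blood-pressure change in one of the 32 of 53 home sessions counts as neither major nor minor unless it is measured by means the article does not name. Other exercise-related symptoms without a confirmed change in vital signs have no class in any setting. The direction of any error is towards too few reported side effects.

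Its size cannot be computed. The range in the working, from no loss to 60% of major-type events uncounted, rests on assumed rates and concerns only the blood-pressure part. A reader might conclude that the harm of the programme *is* understated; the documents support only that it *may* be. The primary comparison of walking distance is not affected.

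**What to change.** 1. Keep the current major class as it is: fall trauma needing intervention, and instrument-confirmed symptomatic vital-sign changes. Nothing that counts as major now should be downgraded.
2. Add a separately reported class for symptomatic events during or shortly after a session that lack instrumental confirmation, and for other exercise-related symptoms. Record confirmation (yes/no) as a descriptor.
3. Add one symptom line to the existing training log and have it checked at the outpatient sessions already scheduled. At two per week, 15 sessions take 7.5 weeks, whereas 24 home sessions at three per week take 8. The log must therefore also be read for the few days after the last outpatient session.
4. Report home and outpatient events separately.

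**Cost.** A protocol amendment and one extra line in the log, with no new visit. Reported counts will be higher and will include unconfirmed symptoms. Enrolment began in 2015, so events before and after the change were collected under different rules and must be reported separately. If the full protocol already has a wider adverse-event record, stating how such events are classed would be enough.
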